# Treatment of supraglottic squamous cell carcinoma with advanced technologies: observational prospective evaluation of oncological outcomes, functional outcomes, quality of life and cost-effectiveness (SUPRA-QoL)

**DOI:** 10.1186/s12885-023-10953-9

**Published:** 2023-06-01

**Keywords:** Head and neck cancer, Supraglottic, Squamous cell carcinoma, Radiotherapy, Transoral robotic surgery, Transoral Laser Microsurgery and Quality of life

## Abstract

**Background:**

Over the past decade, therapeutic options in head and neck supraglottic squamous cell carcinoma have constantly evolved. The classical total laryngectomy has been partially replaced by alternative organ- and function-sparing techniques with the same prognosis but less morbidity, such as Radiotherapy, Transoral Laser Microsurgery (TLM) and Trans-Oral Robotic Surgery (TORS). Up to now, a prospective comparison of these innovant techniques has not been conducted.

**Methods/design:**

We will conduct an original international multicentric prospective nonrandomized clinical trial to compare the efficacy between these treatments (Arm 1: Radiotherapy ± chemotherapy; Arm 2: TLM and Arm 3: TORS) with 4 classes of outcomes: quality of life (QoL), oncological outcomes, functional outcomes and economic resources. The population will include cT1-T2 /cN0-N1/M0 supraglottic squamous cell carcinoma. The primary outcome is a Clinical Dysphagia QoL evaluation assessed by the MD Anderson Dysphagia questionnaire. Secondary outcomes include others QoL evaluation, oncological and functional measures and cost parameters. The sample size needs to reach 36 patients per arm (total 108).

**Discussion:**

In the current literature, no prospective head-to-head trials are available to compare objectively these different treatments. With the increase of highly efficient treatments and the increase of oncological survival, it is imperative also to develop management strategies that optimize QoL and functional results. We will conduct this innovate prospective trial in order to obtain objective data in these two main issues.

**Trial registration:**

NCT05611515 posted on 10/11/2022 (clinicaltrial.fgov).

## Background

Head and Neck Squamous Cell Carcinoma (HNSCC) are the seventh most common cancer worldwide, with approximately 600.000 new cases diagnosed each year [1]. In Supraglottic Squamous Cell Carcinoma (SSCC), total laryngectomy has been the mainstay treatment until the late 80 s’. However, laryngectomies are associated with an important loss of key function such as phonation and swallowing. More recently new organ preservation techniques have emerged, allowing better functional outcomes for patients.

First, partial open laryngectomy is associated to high stable local control rate (around 77%) [2–4] and offers the advantage of a functional larynx preservation rate in 80% of the patients [5, 6]. Due to the cervical access to the tumor, the recovery to safe swallowing takes time with the need of a transitory tracheostomy and a prolonged hospitalization time with parenteral intakes [7]. Aspiration pneumonia rate is around 6% [6].

Secondarily, the development of new radiation techniques (Intensity Modulated Radiotherapy, IMRT) and the concurrent administration of chemotherapy drugs allow better organ preservation and reduce tracheostomy rate [8–10]. The oncological outcomes remain stable, with same regional control of 70% at 5 years [11–13]. Aspiration rate (a dysphagia marker) remains in 14% of reported cases and edema with respiratory problems can occur [14]. In 16.8% of the cases a functional laryngectomy or permanent tracheostomy is required [14]. This can be explained by pharyngeal mucosa and constrictor muscles injury, as well as fibrosis and decreased pharyngeal peristalsis induced by radiation [15–17].

Thirdly, the development of new surgical instruments enables a Trans-oral approach with Laser Microsurgery (TLM). TLM gives a 2-year Overall Survival (OS) of 83% for pT1-T2 tumors, with a larynx preservation in 95% [18, 19]. However in that study, 13% of the patients needed a temporary tracheostomy and 3% kept a gastrostomy at 1 year [18]. The main limitation of TLM is the linear view of the microscope, as well as the laser beams, which requires a piecemeal resection of the tumor in difficult cases [20].

Subsequently, Trans-oral Robotic Surgery (TORS) emerged as an evolution of the TLM [21–24]. The main advantages are the 3D-high-quality camera and the dexterity improvement with 7 degrees of freedom articulated arms [25–27]. Some studies concerning supraglottic location reported a 2-year OS of 89% without the need of tracheostomy or gastrostomy [28, 29]. Patients started oral feeds at an average of 2 weeks [30].

Actually, the current standards of treatment are based on either surgery or radiotherapy. The treatment choice is center-, tumor- and patient-dependent with different side effect profiles and technical constraints [31, 32]. To the best of our knowledge, there is no head-to-head prospective comparison between TLM, TORS and radiotherapy. Moreover, in the available retrospective studies, functional data are often not comparable. In two meta-analyses, the oncological outcomes (OS and Disease-Specific Survival (DSS)) seem to be more favorable for TORS and TLM group (Odd Ratio (OR) 43% and 40%) compared to the radiation group, which is still the mainstay of treatment [14, 33]. Probably, the transoral approaches alone will confirm or even improve functional benefit. The authors concluded that prospective functional studies with objective measures are needed [14, 33].

Concerning the QoL of the patients treated for HNSCC, one prospective study has been published (“ORATOR study” [34]) while another is still ongoing (“Best-of European study”[35]). In the ORATOR study, patients treated with radiotherapy showed superior swallowing-related QOL scores at 1 year after treatment, although the difference did not represent a clinically meaningful change. Moreover, in the TORS subgroup, 71% patients were treated with adjuvant radio(chemo)therapy which makes the results difficult to interpret. However, these two studies investigate exclusively the outcomes of patients with oropharynx squamous cell carcinoma. There is currently no prospective study about the QoL of patients treated for a supraglottic cancer.

The main objective of this trial is to assess and compare objectively and prospectively the efficacy of different therapeutic approaches (radiotherapy ± chemotherapy, TLM and TORS) in SSCC patients according to 4 classes of outcomes; quality of life, oncological, functional and economic resources.

## Methods – design

We propose to carry out an observational non-randomized prospective clinical trial on patients diagnosed with an early SSCC where 3 subgroups are studied in parallel:Arm 1: Radiotherapy ± chemotherapy (RCT)Arm 2: Trans-oral Laser Microsurgery (TLM)Arm 3: Trans-Oral Robotic Surgery (TORS)

The inclusion will be multicentric and international. The treatment will be chosen by the local multidisciplinary tumor board (MTB) according to the primary cTNM-stage, the patient preferences and the local standard of care based on peer-reviewed international guidelines (Fig. 1, SPIRIT Flow Chart and Fig. 2, Trial Design). The guidelines to be followed are the National Comprehensive Cancer Network (NCCN) [31] or the European guidelines including the European Head and Neck Society (EHNS), the European Society of Medical Oncology (ESMO) and the European Society for RadioTherapy and Oncology (ESTRO) [32].

**Fig. 1 Fig1:**
[figure not shown]
SPIRIT Flow Diagram

**Fig. 2 Fig2:**
[figure not shown]
Trial Design

### Inclusion criteria

Diagnosis of SSCC (with histological confirmation)cT1-T2 / cN0-N1/ M0 according to 8.^th^ TNM classification (UICC/AJCC) [36]WITH a MTB decision according to the NCCN or European guidelines [31, 32]Diagnostic imaging (Head and neck and pulmonary CT or PET/CT, ± IRM if needed) realized within 1 month before the study inclusion ≥ 18 years old and able to provide an informed consentECOG/WHO performance status ≤ 2 [37]

All participants must have a writing informed consent before their involvement.

### Exclusion criteria

Previous radiotherapy ± chemotherapy treatment of the head and neck regionPrevious history of head and neck cancer within 5 yearsPrior invasive malignant disease unless disease-free for at least 5 years or more, with exception of non-melanoma skin cancerNon-supraglottic or unknown primary siteClinical and radiological signs of nodal extracapsular extensionSignificant trismus (maximum inter-incisal opening ≤ 35 mm)Pre-existing dysphagia not related to the cancer or the biopsy (from neurological disorders for example)Unable or unwilling to complete Quality of Life questionnairesSerious medical comorbidities or contraindication for surgery and/or radiationPregnancy and lactation

### Primary outcome measure

Clinical Dysphagia QoL evaluation after treatment will be assessed using MD Anderson Dysphagia Index (MDADI) at 1 year [38, 39]. It contains 20 items; ranged in score from 0 to 100 (a high scale score represents a higher response level). Time Frame: baseline (before treatment), 3 – 6 – 9 – 12 – 18 – 24 months after treatment.

### Secondary outcome measures (Fig. 3)

**Fig. 3 Fig3:**
[figure not shown]
Examination planning

#### QoL measures

QoL will be evaluated with the validated European Organization for Research and Treatment of Cancer (EORTC) QLQ-C30 and H&N43 questionnaires ([40–42]. Time Frame: baseline (before treatment), 3 – 6 – 9 – 12 – 18 – 24 months after end of treatment (EOT).

#### Oncological measures

Overall survival, Disease specific survival, Disease-free survival, loco-regional and distant cumulative recurrence rate (%). Time Frame: 24 months from the start of treatment.

Histopathological finding for surgical arms: section margins status (R0/R1 and distance in mm) and P16 or HPV tumor status.

#### Functional measures

- Weight *(Kg).* Time Frame: 6 months before the diagnosis, baseline (before treatment), 1 – 3 – 6 – 9 – 12 – 18 – 24 months after treatment.- CTC-AE score for early and late complications. Time Frame: baseline (before treatment), 1 – 3 – 6 – 9 – 12 – 18 – 24 months after treatment [43, 44].- Naso-gastric Feeding tube and/or gastrostomy use *(duration in days).*- Tracheostomy use (duration in days).*-* Swallowing function by FEES evaluation (Fiberoptic Endoscopic Evaluation of Swallowing) objectively evaluated by the Penetration-aspiration Scale (PAS [45]). Time Frame: baseline (before treatment), 1 – 3 – 6 – 9 – 12 – 18 – 24 months after treatment.- Treatment-related pain with Self-reported Visual Analogue Scale (VAS) and need for pain medication.- Need of hospitalization (if yes, *duration in days*).- Blood Test. Timeframe: Baseline (before treatment) – 3 – 6 – 12 – 24 months after treatments.- ECOG performance status and Charlson Comorbidity Index [37, 46]. Timeframe: baseline (before treatment) – 6 – 12 – 24 months after treatment.

#### Cost measures

To set-up an economic analysis, we will collect resource data along this trial for the different treatment strategies and their complications through database analyses, chart review, patient diaries and EQ-5D-5L questionnaires [47, 48]. The follow-up starts just after the therapy (surgeries or radiation) and ends at 1-year post-intervention. The health care resource use items include acute and post-acute care, length of stay, medication use, outpatient and inpatient hospital visits, laboratory tests, radiology and medical professional visits. Resources used to treat complications will be recorded separately.

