### Interventions

#### Arm 1: Radiotherapy ± chemotherapy (RCT)

Volumetric Modulated Arc Therapy (VMAT) with simultaneous Integrated Boost (SIB) will be used for all patients in this study.

For all cT1-T2N0 tumors, patients will be treated with moderately accelerated radiotherapy alone. Primary Gross Tumor Volume (GTVp) will be delineated according to the clinical examination and the available imaging. A 10 and a 5 mm margins (adapted to anatomical barriers) will be added to generate the Primary Clinical Target Volumes (CTVp) treated at prophylactic and radical (or therapeutic) doses, respectively (according to the current guidelines [49–51]):The therapeutic CTVp includes the tumor area and the high-risk location. It will be irradiated up to a total dose of 69 Gy in 30 fractions (2,3 Gy/fraction, 5 fractions a week during 6 weeks) or 70 Gy in 35 fractions (2,0 Gy/fraction, 6 fractions a week during 6 weeks).The prophylactic CTVp includes the elective mucosa. It will be irradiated up to a total dose of 54 Gy in 30 fractions (1,8 Gy/fraction, 5 fractions a week during 6 weeks) or 54,25 Gy in 35 fractions (1,55 Gy/fraction, 6 fractions a week during 6 weeks).

Elective CTVn must be selected and delineated according to the international recommendations and treated at prophylactic dose [50, 52].

All CTVs will be expanded by an isotropic 3–5 mm margin to generate the related Planning Target Volume (PTV). Margin may be cropped at level of skin for correct optimization and avoiding skin overdosage.

For all cT1-T2 N1 tumors, patients will be treated with concurrent radio-chemotherapy [49–51]. Selected patients with a “small” positive node (I.E., centimetric) or having an absolute contra-indication to chemotherapy may be treated with radiotherapy alone.

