In the case of concomitant chemotherapy, the selection, delineation and prescription will follow the same principles as stated above, except that.Nodal Gross Tumor Volume (GTVn) will be delineated according to the clinical examination and available imaging. A 5 mm margin adapted to anatomical barriers will be added to generate the nodal Clinical Target Volume treated (CTVn), to be treated at therapeutic dose.Only normo-fractionated schedule may be used but may be accelerated at the discretion of the center by use of 6 fractions a week.The standard chemotherapy regimen is the Cisplatin 100 mg/m^2^ on days 1 – 22 and 43 (5 fractions a week) or on days 1 and 22 (6 fractions a week). In case of contra-indication to cisplatin, alternatively, carboplatin-5FU may be administered on weeks 1, 4 and 7 (5 fractions a week) or on weeks 1 and 4 (6 fractions a week). Weekly schedules or cetuximab or any other investigational or non-investigational radio-sensitizing drugs are not allowed.

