Delineation of CTVs and PTVs will follow the same rules. Therapeutic/elective doses will be prescribed to the respective PTVs at 66/56,1 Gy in 33 fractions of 2/1,7 Gy and planned with SIB-IMRT. Concomitant radio-sensitizing chemotherapy with 3-weekly Cisplatin or Carboplatin-5FU will be prescribed following the same rules as for definitive-radiation.

In both cases, every reasonable effort should be made to start the post-operative (chemo)radiation within the 6 weeks after surgery.

In case of recurrence or secondary primaries, a new panendoscopy with biopsy must be performed and the results should be discussed at the MTB. In case of a very small recurrence of secondary primary, a new trans-oral procedure can be performed. In case of a bigger tumor, salvage radiotherapy should be preferred. In case of contra-indication to radiotherapy (e.g., previous radiation on the neck), a total laryngectomy or total pharyngo-laryngectomy is required.

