### Modelling analysis

In addition to the study protocol, we will also carry out a Mathematical MultiState-transition Markov Model to perform long-term cost-effectiveness extrapolation. It will be used in order to extend the time horizon (to a life-time horizon) and to extrapolate the intermediate outcome parameters (e.g., OS and DFS) to outcome parameters (e.g., mortality). Sources will be this trial and a systemic literature review on the outcome parameters as well as the costs from the baseline and beyond the trial horizon. The model design will be a Markov Multistate Cohort Model [69, 70]. To test the robustness of uncertain parameters will be presented with one- and two-way and probabilistic sensitivity analyses (by Monte-Carlo PSA) [71]. Through worst-case scenarios and distributions of the input variables the robustness of the model will be demonstrated with regard to input.

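### The economic follow-up starts at the end of therapy, a time origin that differs by arm and conflicts with the plan's own costing from baseline

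*Protocol article*

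**What the plan says.** Cost measures sets the window: "The follow-up starts just after the therapy (surgeries or radiation) and ends at 1-year post-intervention". The same paragraph gives a wider scope, "we will collect resource data along this trial for the different treatment strategies and their complications", and its item list begins: "The health care resource use items include acute and post-acute care, length of stay, medication use, outpatient and inpatient hospital visits". EQ-5D-5L belongs to this data collection, and the Discussion uses it to derive utilities and QALYs.

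Modelling analysis describes a lifetime Markov model fed by this trial and a literature review. It refers to outcome parameters "as well as the costs from the baseline and beyond the trial horizon".

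In Arm 1 the two radiotherapy-alone schedules are "69 Gy in 30 fractions (2,3 Gy/fraction, 5 fractions a week during 6 weeks" and "70 Gy in 35 fractions (2,0 Gy/fraction, 6 fractions a week during 6 weeks". For node-positive patients treated with chemoradiation, cisplatin is given "on days 1 – 22 and 43 (5 fractions a week) or on days 1 and 22 (6 fractions a week". In Arms 2 and 3 the therapy response section adds adjuvant radiotherapy (30 fractions) or chemoradiation (33 fractions) when pathology is adverse, and asks that "every reasonable effort should be made to start the post-operative (chemo)radiation within the 6 weeks after surgery".

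Other outcomes use other origins. Oncological measures run from the start of treatment, and the Statistical analysis section counts survival from the date of the tumor board (MTB).

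**The concern.** An economic comparison needs the same clock in every arm. Here the clock starts when therapy ends. In one arm that is the end of a course lasting several weeks. In the other two it is the end of an operation. Similar kinds of care then fall on different sides of the starting line. A radiotherapy course can be counted when it is adjuvant and not when it is definitive. Inpatient care after surgery is counted, while toxicity care during radiation is not.

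Cost-effectiveness is in the title and is one of the four declared outcome classes. The trial's costs and utilities also feed the Markov model, which extrapolates survival counted from the MTB date or the start of treatment. If costs start later than survival, and later by a different amount in each arm, the model joins inputs that do not share a time zero.

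**Working it through.** The document gives no figure for the economic analysis, no unit costs and no adjuvant rate for this trial. The check is therefore a timeline in weeks from the start of treatment.

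**Course length** = fractions ÷ fractions per week.
- 30 fractions at 5 a week: 30/5 = 6.0 weeks, as stated.
- 35 fractions at 6 a week: 35/6 = 5.8 weeks, consistent with the stated 6.
- 35 fractions at 5 a week (non-accelerated chemoradiation): 35/5 = 7.0 weeks. Day 43 opens week 7 (6 × 7 + 1), so the third cisplatin date lies within the course.

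**Reading A: therapy means the index treatment.** The window runs from the end of the index treatment to 52 weeks later.

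| | Window (weeks) | Before the window | Inside the window |
|---|---|---|---|
| Arm 1, 30 at 5 a week | 6.0 to 58.0 | all 30 fractions, care during the course | later care |
| Arm 1, 35 at 6 a week | 5.8 to 57.8 | all 35 fractions, any chemotherapy, care during the course | later care |
| Arm 1, 35 at 5 a week | 7.0 to 59.0 | all 35 fractions, chemotherapy, care during the course | later care |
| Arms 2 and 3 | about 0 to 52 | index operation (theatre, laser or robot) | post-operative stay, adjuvant treatment |

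Adjuvant treatment that starts by week 6, at an assumed 5 fractions a week, ends by 6 + 30/5 = 12.0 weeks or 6 + 33/5 = 12.6 weeks. It lies wholly inside the surgical window.

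Mean fractions counted per surgical patient = adjuvant share × 30 to 33. The share is an assumption, shown over its full range. The 71% is the figure the Background quotes for the robotic arm of an oropharynx trial, so it need not apply here.
- 0%: 0
- 30%: 9.0 to 9.9
- 50%: 15.0 to 16.5
- 71%: 21.3 to 23.4
- 100%: 30 to 33

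The index fractions counted in Arm 1 are 0 throughout.

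**Reading B: therapy includes planned adjuvant treatment.** Surgery-only patients start at about week 0. Patients given adjuvant treatment start at about week 12.0 to 12.6 under the same assumptions. Their post-operative stay is then dropped, although length of stay is a listed item. The origin now differs among surgical patients as well as between arms.

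**Reading C: the sentence describes only the follow-up phase, and index treatment is costed as well.** Costs then start together, but one year post-intervention still ends at about week 58 to 59 in Arm 1 and week 52 after surgery alone. The accounting periods differ by 6 to 7 weeks, this time with Arm 1 counted for longer.

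None of the three readings gives the arms the same period.

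**The case against.** The strongest reply is that one sentence is being read against its own paragraph. Collecting resources for the treatment strategies implies that the treatments are costed, and the modelling section's reference to baseline points the same way. Functional measures also lists feeding-tube and tracheostomy days, hospitalization days and pain medication without a post-treatment time frame, so part of the on-treatment use in Arm 1 may be recorded anyway. Counting adjuvant radiotherapy inside the window depends on how therapy is understood. The article is also condensed, and detailed costing rules usually sit in a fuller document.

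Much of this stands, and it limits the point. A reader might infer that the plan favours radiotherapy by construction. The document does not support that: on the same literal reading the index operation, including theatre and robot use, is also left out, and no unit costs or adjuvant rate are given to net one omission against the other. A reader might also turn the 6 to 7 weeks into 6/52 to 7/52 of a year (11.5% to 13.5%) and attach a QALY loss. The Arm 1 window is shifted, not shortened, and any on-treatment utility decrement would be an assumption with nothing set against it in the surgical arms. Nor can one say that a pre-treatment EQ-5D-5L is missing. The examination schedule is in Fig. 3, which is not shown, and the MDADI and EORTC questionnaires do have baseline assessments.

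The reply does not remove the stated rule. The article could have left the time origin to another document. It fixes one instead, and that origin depends on the arm and disagrees with the scope given in the same paragraph and with the modelling section.

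**Conclusion.** The point holds as a badly fixed time origin for one of the four declared outcome classes. As written, the economic window opens about 6 to 7 weeks after the start of treatment in Arm 1 and at about week 0 in the surgical arms. It leaves out index treatment in every arm and counts the post-operative stay and adjuvant (chemo)radiation. The other readings change which care is misaligned but do not make the arms comparable.

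This can bias the between-arm comparison of cost and QALYs and carry over into the Markov model. Size and direction cannot be determined from the document. The timeline rests on the stated schedules, on 5 adjuvant fractions a week (assumed) and on adjuvant treatment starting by the 6-week target. The primary outcome and the sample size are not affected.

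**What to change.** In Cost measures, replace the sentence on the start and end of follow-up with one common origin for resource use and EQ-5D-5L/QALYs in all arms: either the MTB decision date or the first treatment day. Set one common elapsed end from that origin. State that index-treatment and on-treatment resources are included in every arm, with adjuvant treatment counted in the same way. Use a pre-treatment EQ-5D-5L as the utility baseline, and confirm that the Fig. 3 schedule contains it. Align the Modelling analysis section with this origin, and state how it relates to the survival time zero, which is itself given as the start of treatment in one section and the MTB date in another.

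The cost is small: a wording change and some extra data entry, mainly on-treatment items in Arm 1 and index-procedure items in the surgical arms, from charts whose review is already planned.
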